**Translated protocol version 6**

**May 11, 2017**

**Authors**

[name]^1^

E-mail: [contact]

[name]^1, 2^

E-mail: [contact]

[name]^1^

E-mail: [contact]

[name]^1, 2^

E-mail: [contact]

[name]^1^

E-mail: [contact]

[name]^3^

E-mail: [contact]

[name]^4^

E-mail: [contact]

[name]^1^**^*^**

^1^Department of Anesthesiology, University Hospital RWTH Aachen, [name], Germany

^2^ Emergency Medical Service, Fire Department, [name], Germany

^3^Emergency Department, University Hospital Aachen, [name], Germany.

^4^Department of Medical Statistics, University Hospital RWTH Aachen, [name], Germany

| **Originally approved protocol version** | **Date approval by ethics committee; No.** |
| --- | --- |
| Version 3; November 11, 2015 | November 25, 2015; EK 170/15 |

| **Protocol changes** | **Summary of changes** |
| --- | --- |
| Version 4; June 13, 2016 | - 90 days follow-up was added. |
| Version 5; September 2, 2016 | - 1.5-2 months lasting “Run-in” phase was prepended.  - Added retrospective analysis of all EMS cases, which were excluded according to the exclusion criteria and treated by a conventional EMS physician during the study period.  - Extension of the main study period to 8-10 months with the earliest beginning after December 01, 2016.  - Addition that the retrospective analysis is performed pseudonymised and without patient informed consent.  - Addition of [name] as an investigator. |
| Version 6; May 11, 2017 | - New sample size calculation was added. New sample size comprises 3344 patients.  - “Non-inferiority” wording was specified in the objectives.  - It was specified that the data safety board members receive blinded data, unless the total number of adverse events exceeds 6%.  - The number of needed patients for the first and second interim analysis was adapted according to the new sample size.  - Change of randomisation process into an automatised process, which is implemented in the dispatching software. |

**Abstract**

**Background**

Increasing number of emergency calls, shortages of Emergency Medical Service (EMS) physicians and prolonged emergency response times with delay and regional different quality of treatment by EMS physicians, require an improvement of this system. Telemedical solutions were shown to be beneficial in different emergency projects, focused on specific disease patterns. Our previous pilot studies have shown that the implementation of a holistic pre-hospital EMS teleconsultation system, between paramedics and experienced tele-EMS physicians, is safe and feasible in different emergency situations. We aim to extend the clinical indications for this teleconsultation system. We hypothesise that the use of a tele-EMS physician is non-inferior in regard to the occurrence of system-induced patient adverse events and superior in regard of secondary outcome parameters such as guideline-conform treatment- and documentation-quality when compared to the conventional EMS physician treatment.

**Methods/ design**

3344 patients will be included in this single-centre, open label, randomised controlled, non-inferiority trial with two parallel arms. According to the inclusion criteria, all emergency cases of adult patients, who require an EMS physician treatment, excluding life-threatening cases, will be randomly assigned by the EMS dispatching centre into two groups. 1672 patients in the control-group will be treated by a conventional EMS physician on scene, and 1672 patients in the intervention-group will be treated by paramedics, which are concurrently instructed by the tele-EMS physicians of the teleconsultation centre. The primary outcome measure will include the rate of treatment-specific adverse events depending on the used kind of EMS physician. The secondary outcome measures will record the specific treatment associated quality indicators.

**Discussion**

Evidence underlines better quality of supply with telemedicine networks between medical personnel and medical experts in pre-hospital emergency care, as well as in other medical areas. The worldwide unique EMS teleconsultation system of Aachen was optimised and evaluated in pilot-studies and subsequently integrated in the routine use for a broad spectrum of indications. It enabled prompt, safe and efficient patient treatment with optimised use of the "resource" EMS physician. There is a lack of evidence, whether the advantages of the teleconsultation system could be confirmed in wide-ranging EMS physician indications (excluding life-threatening-emergency calls).

**Trial registration**

ClinicalTrials.gov: NCT02617875, registered November 24, 2015

**Background**

The German and some other European Emergency Medical Services (EMS) consist of a dual system with two paramedics (professional education of two years) and one EMS physician accompanied by a further paramedic. The emergency call is received by the EMS dispatch centre and answered by a specially trained paramedic [1], who dispatches either solely an ambulance vehicle with paramedics or simultaneously, in life-threatening cases, also an EMS-physician vehicle. This is called the rendezvous system. If only an ambulance vehicle was dispatched, but the on-site patient situation requires an EMS physician (e.g. more life-threatening case, or a special medication like opioid analgesia for severe pain management or a drug to reduce systemic arterial pressure in case of severe arterial hypertension is required), then an EMS physician can be demanded by the paramedics on site. The German nationwide network of ambulance vehicle locations shows a significantly higher density than the emergency physician locations [2]. This is due to the fact that the national law and local regulations of the 16 states of Germany define the maximal time frame for the EMS aid in Germany. Hence, the paramedics usually arrive several minutes earlier than the EMS-physician on the emergency scene. The paramedics have to start with the primary emergency medical care on their own authority, but within the restrictions of the German law and local regulations. The time delay until the arrival of the EMS-physician is more pronounced in rural than in urban areas and can jeopardise the patients by omission of physician dependent treatments. Increasing number of emergency calls, of vacant EMS physician sites due to lack of emergency physicians, and increasing loads of the EMS physicians, hinder the disposability of EMS physician treatment [3]. Paramedical teams solely cope 56% of the current emergency calls in Germany, the remaining 44% require an additional EMS physician [2]. This ratio depends on the region and the ratio shifts to more EMS-physician requirements in rural areas in comparison to urban areas. Furthermore, the arrival time of the EMS physician to the emergency scene has become considerably prolonged in 95% of the emergency cases during the last twenty years in Germany [4-6]. This time interval increased from 18.9 to 28.2 minutes in the years 1995 to 2012 and it was more than 20 minutes in 17% of the cases in 2012. The obligatory EMS response time in the German state of North Rhine-Westphalia of 8 minutes for the first EMS unit in urban areas, and 12 minutes in rural areas is based on the recommendations according to the law (RettG NRW). These data reveal that the time interval between the arrival of the EMS ambulance and the EMS physician is frequently prolonged. In addition, as recently shown in the German state of Rhineland-Palatinate, some EMS physician sites do not provide continuous operational readiness due to shortages of physicians [7]. Although there is a lack of systematic data for all German states, it is obvious that similar conditions are throughout present, especially in rural German areas. In these cases EMS physicians from farther away locations or helicopter emergency medical services mostly during the daytime become required. This circumstance further implies prolonged response times of EMS physicians and the solely restricted treatment by paramedics until their arrival. In many cases the paramedics are not able or not allowed to administer adequate aid (i.e. administration of opioids or invasive procedures) [8].

In summary, Germany has a well established ground based EMS, but five problems remain:

- Prolonged emergency response times with delayed treatments by EMS physicians
- Increasing numbers of emergency calls
- Shortages of EMS physicians
- Out-dated communication systems
- Regional different and improvable emergency treatment quality

**Mobile pre-hospital EMS teleconsultation**

Telemedicine networks between medical personnel and medical experts were shown to be beneficial for the quality of supply in many medical fields. National and international teleconsultation is increasingly used for emergency care of stroke patients between hospitals with and without specialised stroke units [9-13]. Hereby it was shown that the real-time use of digital observation cameras was more favorable than the telephone-consultation [12,13]. Furthermore, transmission of a pre-hospital 12-lead electrocardiogram (ECG) and telephone-consultation with a cardiologist improved the emergency treatment and the outcomes of acute myocardial infarction patients [14-18]. Other pre-hospital teleconsultation systems in emergency medicine are rare and were only used in pilot-projects [19,20]. The American Heart Association (AHA) emphasised the use and scientifically evaluation of teleconsultation systems in the pre-hospital emergency care [21-23]. The German research project "Stroke Angel" showed that the use of a tablet computer, with structured collection of stroke-specific patient data and the automatically forwarding to the hospital, decreased the pre-hospital process time of acute stroke management to the half [20]. One disadvantage of this concept is the very specific focus on one medical condition.

The obvious need for a safe and broad usable tele-emergency system stimulated us to develop a holistic multifunctional, algorithm-based, mobile teleconsultation system, as a complementary structural element to the ground based and air based EMS.

**Routine use of the EMS teleconsultation system in Aachen**

After the favorable experience during the two pilot studies [19,24], the EMS teleconsultation system was step-wise introduced in the routinely use, complementary to the ground and helicopter based EMS of Aachen. Since 2014 the costs are covered by the health insurance funds. All ambulance vehicles are equipped with the teleconsultation system since 2015. Up to day the teleconsultation EMS physician (tele-EMS physician) is mainly used for distinct cases such as hypertensive emergency, stroke, dislocated fractures, which are originally dispatched only to the paramedics. The decision to involve a tele-EMS physician is made by the paramedics on scene based on standard operating procedures (SOP) by the EMS medical director, after verbal informed consent of the patient. Additionally, the paramedics decide on their own, whether they demand a physically present EMS physician on scene. Therefore the tele-EMS physician is used either during the time gap until the arrival of the physically present EMS physician or the tele-EMS physician provides medical and organisational advice without a physically present EMS physician. This offers the opportunity for the paramedics to administer medications and perform invasive procedures under the supervision by the tele-EMS physician, which is otherwise not possible by national laws and local regulations. For example paramedics are not allowed to administer opioids without a delegation by a physician. If adverse events (AEs) occur, the tele-EMS physician can give an advice to prevent possible consecutive damages. The teleconsultation system in Aachen protects the patients from delayed physician-dependent treatments and provides a high-quality medical therapy by using software–based guideline conform treatment. A delegation of in-hospital opioid application by physicians to nursing stuff is usual, but unusual in EMS. Severe pain or other threatening conditions require a prompt and accurate medical treatment. In one pilot study, conducted in the EMS of the central State of Hessen, an EMS physician delegated by phone the morphine application by paramedics in 172 patients with limb trauma. This resulted in no threatening AEs and the pain could be significantly reduced [25]. In contrast to the in-hospital delegation by phone and in the latter study, the tele-EMS physician in Aachen monitors (ECG, pulse oxymetry, blood pressure measurement, voice communication with the paramedics) the patient continuously during the treatment until the patient is handed over to a further physician (EMS physician or physician in hospital). This system holds the potential to improve patient safety with online medical control of the paramedics. Concurrently the obligatory indications for dispatching of an EMS physician were confined since March 2015, as a tele-EMS physician is available at any time. This refers for example to the emergency cases, where the decision for drug application is required. Meanwhile 4219 patients (1 April 2014 – 31 March 2016, worldwide the largest case series) were routinely treated with this EMS teleconsultation system in Aachen. Until now, the primary dispatching of the tele-EMS physician was waived. But, analysis of the severity level of the EMS responses by paramedics with the secondary use of the tele-EMS physician shows similar severity levels as the primary dispatched EMS physician staffed responses. Furthermore, the use of the tele-EMS physician instead of a conventional EMS physician did not show any complications and the quality of the medical history survey, the medical treatment and the documentation of "Tracer" diagnoses like stroke and myocardial infarction improved. Also the engagement time of the physician decreased to the half with the use of the teleconsultation EMS. Our experience from the routine use of the teleconsultation EMS system in Aachen - excluding critical emergency cases like severe trauma, cardiopulmonary resuscitation and advanced airway management - shows that this system may provide an equal or even better quality of care than the conventional EMS system. Furthermore, this system enables more economical utilisation of the EMS physician resources. A nationwide implementation of this teleconsultation EMS system in all dual EMS systems requires the proof that it is not causing harm and shows some advantages in cases of primary tele-EMS physician dispatching (excluding life-threatening emergency calls).

**Objectives and study design**

The TEMS trial is designed as a single-centre, prospective, randomised interventional, open label, two-arm parallel group sequential, non-inferiority trial (Fig. 1). The purpose of this trial will be to assess:

- The quality of pre-hospital emergency care using the multifunctional teleconsultation system between paramedics and experienced tele-EMS physicians.

**Specific primary objective**

To determine if the primary usage of a tele-EMS physician compared to a conventional EMS physician on scene, in non-life-threatening cases, is non-inferior with regard to the occurrence of system-induced patient AEs.

**Specific secondary objective**

To determine if the primary usage of a tele-EMS physician compared to a conventional EMS physician on scene, in non-life-threatening cases, is superior in regard to the quality of the medical history survey, medical treatment and documentation.

**Other secondary objectives**

- To determine the different durations between the emergency call, the emergency response by a physician and the arrival time in the hospital.
- To determine the National Advisory Committee for Aeronautics (NACA) score classifications of the treated patients.
- To determine the number of emergency cases, which were handed over to the tele-EMS physician.
- To determine the number of additional requirements of EMS physicians on scene in the case of primary dispatched tele-EMS physicians.
- To determine the technical performance.
- To determine the direct costs involved in the two systems.
- To determine the acceptance of the teleconsultation system by the paramedics, the EMS physicians, the patients and the emergency room personnel.
- Parallel to the randomised main study, we aim to retrospectively analyse all EMS cases, which were excluded according to the exclusion criteria and treated by a conventional EMS physician during the study period.
- To determine the frequency of tele-EMS physician consultation by a conventional EMS physician.
- To analyse additional data, which will be collected during a prepended "Run-In" phase of 1.5-2 months.

**Methods**

**Study setting and design**

This prospective single-centre, randomised interventional, open label, two-arm parallel group sequential trial will be conducted in the urban EMS of Aachen, Germany. This study protocol is reported according to the SPIRIT statement and the SPIRIT checklist is provided in the Additional file 1.

**Eligibility criteria**

**Patient inclusion criteria:** All non-life-threatening emergency calls, which do not obligatory require an EMS physician on scene and which do not solely require an ambulance vehicle staffed with paramedics, will be included in this study. This results in the following case for randomisation:

- An emergency call is received by the EMS dispatching centre Aachen. The EMS dispatching personnel decides after structured interview of the caller, that there is not a life-threatening situation (according to the exclusion criteria), but a physician is required in addition to the paramedics.

**Patient exclusion criteria:**

All life-threatening emergency cases, where a physically present EMS physician on scene is obligatory required according to German regulations. These include patient condition and emergency case related indications:

a) Patient condition related indications:

- Apnoea
- Acute respiratory failure
- Cardio-circulatory arrest
- ST-elevation myocardial infarction (STEMI)
- Unconsciousness
- Persistent seizure
- Life- threatening rhythm disorder
- Major trauma
- Complex psychiatric disorders
- Age < 18 years

b) Emergency case related indications

- Major vehicle accident
- (Traffic) accident with children
- Fall from a height (> 3m)
- Gunshot-, stab-, or blow injuries in the head, neck and torso area
- Fires with reference to personal injury
- Explosion-, thermic or chemical accidents with reference to personal severe injury
- High-voltage electrical accident
- Water connected accidents (drowning-, diving accident, fall through ice)
- Accidents involving hazardous goods
- Hostage-taking, rampage or other crimes with potential danger for human life (preventive deployment, police consultation)
- Immediate threatening suicide
- Immediate forthcoming delivery or preceding delivery

**Requirement of telemedical facilities**

All routinely used EMS ambulance vehicles of Aachen are equipped and connected to a specific teleconsultation centre. This system consists of four sections: The teleconsultation centre, a server infrastructure, a fix-mounted in vehicle PC and a portable autonomous communication device called the “PeeqBOX", as previously described [26,27].

**Teleconsultation centre**

The teleconsultation centre is staffed with experienced EMS physicians from the Department of Anesthesiology of the University Hospital of RWTH, Aachen, Germany and physicians of the P3 Telehealthcare GmbH, Aachen, Germany. During the clinical routine one 24/7 tele-EMS physician is required. In the course of this study an additional tele-EMS physician will be engaged. Minimal educational requirement for tele-EMS physicians comprises a minimal experience of 4 years in anesthesiology and intensive care medicine and an EMS physician certification, furthermore additional qualifications like European Resuscitation Council Provider and Pre-Hospital Trauma Life Support. All tele-EMS physicians have to pass a specific training with regard to the telemedical characteristics including communication principles. The teleconsultation centre is located next to the dispatching centre of the region Aachen. Live vital data (curves and numerical data of ECG rhythms and if needed 12-lead ECG, pulse oxymetry, end-tidal CO_2_ concentrations, blood pressure measurements) are transmitted to the tele-EMS physician. Solely the data transmission systems of the company GS Stemple (Kaufering, Germany), which are approved according to the medical devices law, are used. In addition to this diagnostic data, still picture transmission and video transmission data are available to the tele-EMS physician. These data are explicitly used additionally to the verbal communication with the paramedics and not for determination of diagnosis. The content of this visual data has to be verbally verified. SOP, guidelines and drug databases are IT-based provided to the tele-EMS physician. Standardised, context-sensitive and checklist-based documentation software is used in the teleconsultation centre for all emergency cases conducted with the aid of a tele-EMS physician. Data transfer from the emergency scene, respective the ambulance vehicle to the teleconsultation centre, as well as the bidirectional audio connections are encrypted according to the state of the art. This enables highest degree of interception protection during data transmission. To further improve data safety, all data are marked with an electronic key. This key verifies the authenticity of incoming data in the teleconsultation centre and only accurate data become presented. Data storage occurs on specially secured servers with restricted access, only permitted to the medical project management. Video data are not stored, but only streamed.

**General interventions for all patients**

The patients will be randomised into two groups according to Fig. 1.

1.) Conventional EMS

A physically present conventional EMS physician on scene will treat the patients according to the memorised or carried along written SOP.

2.) Teleconsultation EMS

The patients will be treated by the paramedics, which are concurrently instructed by the tele-EMS physicians of the teleconsultation centre according to the IT-based SOP, guidelines and drug databases.

**Interventions—modifications**

A premature discontinuation of the randomised treatment in a patient is only possible for the teleconsultation EMS group in three situations:

1.) If a relevant technical defect occurs, the teleconsultation will be discontinued. A repair attempt of the teleconsultation system should be omitted during the patient treatment. A conventional EMS physician will be dispatched immediately. A technical repair and diagnosis can follow after termination of the emergency case.

2.) If a patient waives the initially issued informed consent, after the beginning of the teleconsultation treatment, a conventional EMS physician will be dispatched immediately.

3.) If a situation develops within the treatment period which requires a conventional physician according the exclusion criteria, a conventional EMS physician will be dispatched immediately.

In the event of modifications or discontinuations of the study treatment, study participants will be retained in the study to enable data collection and preclude missing data.

**Outcomes**

Participant timeline is shown in Fig. 2.

**Primary Outcome Measures**

The primary outcome measure will include the rate of AEs depending on the specific treatment by an EMS physician or tele-EMS physician. A clinical endpoint committee (CEC) will perform the endpoint adjudication by blinded evaluation and assignment of AEs into intervention-related AEs, according to predefined criteria.

These intervention-related AEs are defined as follows:

- Immediate allergic reaction to drug application due to incorrect survey of patients` medical history (omission of the question for drug allergies).
- Intervention-related and immediate treatment-requiring blood pressure drop on scene (e.g. after wrong drug dosage or drug selection).
- Immediate intervention-related apnoea or respiratory insufficiency on scene (e.g. after wrong drug dosage or drug selection).
- Intervention-related circulatory arrest within 24h of EMS treatment (e.g. after wrong drug dosage, drug selection, or wrong hospital referral).

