**Blinding**

Blinding of the dispatching personnel, the paramedics on scene, patients and the physicians is not possible due to practicability reasons. Furthermore the electronic case report form (e-CRF) entering personnel cannot be blinded. The outcome assessors of the late follow-up variables and the CEC for the primary endpoint adjudication will be blinded to the kind of EMS intervention. The data safety monitoring committee (DSMC) will primarily be blinded. Only if the total number of all AEs exceeds 6%, the DSCM will not be blinded due to safety reasons.

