**Statistical methods**

To prove the non-inferiority hypothesis that the system-induced patient AE rate by the treatment of the tele-EMS physician compared to the conventional EMS physician is not inferior by 1.5% of the (1-α)% confidence interval for rate differences will be calculated accounted for the interim analysis (Table 1). The hybrid analysis population as developed by Sanchez will be used as analysis population [29]. Further details will be given in the trial statistical analysis plan, before database lock. The secondary dichotomous parameters will be tested by chi-square test, the continuous parameters by t-Test assuming heterogeneous variances. A subgroup analysis will be performed according to the level of medical education/ experience of the involved physicians in each group.

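### The objective concerns system-induced harm, but the non-inferiority test counts only events that a blinded committee judges intervention-related; the remaining events get only a chi-square test

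*Protocol*

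**What the plan says.** **The question.** The Specific primary objective asks whether primary use of the tele-EMS physician "is non-inferior with regard to the occurrence of system-induced patient AEs". The Abstract and Statistical methods use the same term, system-induced, and Statistical methods attaches the 1.5% margin to it.

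**What is counted.** Under Primary Outcome Measures, "The primary outcome measure will include the rate of AEs depending on the specific treatment by an EMS physician or tele-EMS physician". The committee "will perform the endpoint adjudication by blinded evaluation and assignment of AEs into intervention-related AEs, according to predefined criteria". Four event types qualify:
- an immediate allergic reaction due to faulty history-taking, explained as "omission of the question for drug allergies";
- a blood pressure drop on scene that needs immediate treatment;
- apnoea or respiratory insufficiency on scene;
- the fourth item, "Intervention-related circulatory arrest within 24h of EMS treatment (e.g. after wrong drug dosage, drug selection, or wrong hospital referral").

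The second and third must also be intervention-related; their examples are a wrong drug or a wrong dose.

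**Who decides.** Under Blinding, "the CEC for the primary endpoint adjudication will be blinded to the kind of EMS intervention". The Clinical Endpoint Committee section repeats that the members are blinded and that their task is to sort the four events into intervention-related or not.

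**What happens to the rest.** Secondary Outcome Measures lists adverse events that are independent of the kind of EMS care, and other intervention-related events. Deaths and the time of first physician contact are under Other Outcome Measures. In Statistical methods, "The secondary dichotomous parameters will be tested by chi-square test".

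**The concern.** System-induced and intervention-related are never equated or defined against each other. The protocol describes ways in which the care system itself, as distinct from a drug or history-taking error, could harm a patient. The Background says that the delay until the on-scene physician arrives "can jeopardise the patients by omission of physician dependent treatments". Interventions—modifications allows for technical defects in the tele arm. Harms says that delegation to paramedics is not allowed when data transfer is poor and continuous monitoring is medically indicated. These circumstances differ between the arms by design, yet no primary component names any of them.

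The blinding adds to this. A committee that does not know whether the physician was present, remote or on the way will find it hard to attribute an apnoea or an arrest to that circumstance. Blinded adjudication is good practice in an open-label trial. The difficulty comes from combining it with a causal judgement that may need the very information that is withheld.

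At stake is the meaning of the main conclusion. A non-inferiority statement about system-induced harm would rest on a subset of events from which system-level harm may largely be filtered out.

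**Working it through.** **1. The plan's sample size reproduces.** Inputs from Sample size and Table 1: 2% in both arms, margin 1.5 points, one-sided 2.5%, power 80%, 1:1, Farrington–Manning. The restricted rates under the null are 2.995% and 1.495%.

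- s0 = √(0.02995×0.97005 + 0.01495×0.98505) = 0.2093
- s1 = √(2×0.02×0.98) = 0.1980
- n = [(1.960×0.2093 + 0.842×0.1980)/0.015]² ≈ 1478.5 per arm, as stated

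The stated group-sequential size is 1504.2 per arm, a ratio of 1504.2/1478.5 = 1.017. The Table 1 bounds give cumulative alpha 0.0003, 0.0072 and 0.0250 and final power 0.800, also as stated. The arithmetic is not in question; the point is what is counted.

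**2. How far the attribution filter could matter (assumed shares).** The documents give no rate for unattributed harm. Take 1505 per arm, 2% attributed events in control, the three looks of Table 1, and a true tele excess of which only a share is adjudicated as intervention-related. The tele rate seen by the primary test is then 2% + share × excess.

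| Share attributed | P(non-inferiority), true excess 1.5 points | P(non-inferiority), true excess 3 points |
|---|---|---|
| 100% | 2.5% | about 0% |
| 75% | 9.1% | 0.1% |
| 50% | 25.2% | 2.5% |
| 25% | 52.1% | 25.2% |
| 0% | 79.9% | 79.9% |

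The bottom row equals the planned power, because the primary test responds only to attributed events. For the same reason, an unattributed excess in the conventional arm would not show as a tele advantage.

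**3. What a chi-square test on all events can say.** The 95% half-width for a rate difference is 1.96 × √[(p1(1−p1) + p2(1−p2))/n], with n = 1504 per arm:

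- 2% v 2% (the primary): 1.96 × √(0.0392/1504) = 1.00 point
- 4% v 4% (assumed): 1.96 × √(0.0768/1504) = 1.40 points
- 6% v 6% (assumed): 1.96 × √(0.1128/1504) = 1.70 points

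Take invented counts of 60/1504 (3.99%) conventional and 80/1504 (5.32%) tele. The difference is 1.33 points, and the chi-square statistic is 3.00 (p = 0.083), so the test is not significant. The standard error is √[(0.0399×0.9601 + 0.0532×0.9468)/1504] = 0.00768, which gives a 95% interval of −0.18 to 2.83 points. The test reports no difference, while the interval reaches almost twice the margin. The interval carries the information that a safety reader needs; the p-value does not.

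**The case against.** **Most of the definition is open.** Three of the four components give their examples with e.g., and these include wrong hospital referral. The allergy component is itself an omission. The arms are called intervention groups, so intervention-related can be read as related to the EMS system, and Harms says the primary events are expected in connection with the specific kind of care. The committee's predefined criteria are not reproduced in full. This stands against the stronger inference that harm from delay or omission cannot count. The documents support only that it is not named and is unlikely to be attributed under blinding.

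**The direction is unknown.** A reader might infer that the filter favours the tele arm. The Background sentence on delay concerns the wait for the conventional physician, and the section on routine use says that teleconsultation protects patients from such delay. Uncounted harm could lie in the control arm. This stands, and the point is made for both directions.

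**The data are collected.** Unrelated events, conversions, deaths and contact times are recorded, and the safety committee receives both related and unrelated events. Harm is therefore visible. But no non-inferiority assessment uses these data, and the one test the protocol names for them is unsuited to showing absence of excess harm.

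**The analysis plan may say more.** It may add supportive analyses, and their absence here would be no finding. However, the protocol itself fixes the mismatch of terms, the attribution rule and the chi-square test.

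**Two further readings fail.** Comparing the 2% planning rate with the 6% unblinding trigger, to argue that two thirds of events fall outside the primary, sets a safety threshold for all adverse events against a planning rate for a different set. Making the claim conditional on an all-event interval that is not wholly above zero would bring the significance test back. By normal approximation at 1504 per arm, about 29% of trials with true rates of 4% v 6%, and about 51% with 4% v 5.5%, would still pass.

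**Conclusion.** The point holds in a limited form. The objective and hypothesis are wider than the endpoint. Attribution is made blind to the care system, and the events left over get a test that cannot support a statement about absence of harm. A difference between the systems in harm from delayed, withheld or interrupted physician care, in either direction, could go unseen by the non-inferiority test.

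The size depends on a quantity the documents do not give, namely the share of any excess that the committee would attribute. For a true tele excess equal to the margin, the chance of declaring non-inferiority runs from 2.5% with full attribution, through about 25% at half, to about 80% at none. These are illustrations of the mechanism and not estimates of what will happen. Nothing in the documents shows that tele care causes more unattributed harm. The sample size, the margin and the blinded primary endpoint are not challenged.

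**What to change.** 1. Keep the blinded, committee-attributed endpoint as primary, with its margin and sample size.
2. In Statistical methods, replace the chi-square test for the adverse-event item with a pre-specified supportive analysis. Count the four event types regardless of attribution, by allocated arm, and report the tele-minus-conventional rate difference with a confidence interval shown against the 1.5-point margin.
3. Label this analysis as not powered: the 95% half-width is about 1.4 to 1.7 points at assumed all-event rates of 4% to 6%, against 1.0 for the primary at 2%. Attach no pass/fail condition to it.
4. Use one term for the harm in question in the Abstract, Specific primary objective, Primary Outcome Measures and Statistical methods.
5. Limit the non-inferiority conclusion to adverse events adjudicated as intervention-related, and always report it together with the all-event interval.

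The cost is protocol wording, one extra and wider interval on events already to be collected, and a slightly narrower claim. No extra patients or procedures are needed.
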